### Inclusion criteria

The inclusion criteria are:

Patients ≥18 years who have already had a first Propess®, within 24 to 36 h (before signing the consent) because of medical indications, a term pregnancy (> 37 WG), unfavorable cervical condition (Bishop score < 6), and intact membranes 1 h before inclusion. The fetus must be in cephalic presentation and the patient affiliated with a French social security scheme. Patients must sign the consent form.

### Exclusion criteria

The exclusion criteria are:
multiple pregnancy,prior uterine scar (previous cesarean deliveries or myomectomy)any contraindications to the epidural anesthesia,contraindications to Propess® (a recent history of pelvic inflammatory disease or PG hypersensitivity)abnormal uterine contractility or an abnormal fetal heart rate triggering the removal of the first Propess®, or any adverse effect while the first Propess® is in place (anaphylactic shock or disseminated intravascular coagulation).contraindications to Syntocinon® (oxytocin hypersensitivity, any cardiovascular disorder, or severe toxemia of pregnancy)induction of premature membrane rupture,fetus with intrauterine growth retardation (< 3rd percentile) or macrosomic presentation (> 97th percentile),severe abnormal fetal heart rateinduction due to fetal death in utero, medical termination of the pregnancy, or fetus presenting a lethal fetal pathologypatients under guardianship or curatorship or in custody.

### Trial design

This is a multicenter, randomized, open-label, superiority trial with two parallel arms.

If labor has not commenced 24 h after placement of the first Propess®, patients will be asked to give written informed consent and then will be electronically randomized by a study investigator (doctor) to the control (oxytocin and peridural analgesia if the patient wishes) or experimental (a second 24-h Propess® prior to oxytocin if necessary and peridural analgesia if the patient wishes) group. Written informed consent will be obtained from all participants by a study investigator (doctor) before randomization.

Randomization (ratio 1:1) will be carried out centrally via the Center for Epidemiology, Biostatistics and Research Methodology (CEBIMER) computer platform (Ennov Clinical®) accessible 24 h a day, 7 days a week. To randomize a patient, the investigator must connect to the platform (secure connection) and after a phase of verification of the eligibility criteria, the randomization will be performed automatically.

The allocation will be performed by minimization, which provides similar distribution of selected factors between control and experimental groups. Randomization lists are not set up in advance and the first participant is randomly allocated. For each following participant, the treatment allocation that minimizes the mismatch on the five selected factors between groups will be identified.

It will be a randomization by minimization on the following factors:
Bishop’s score (< 3, 3–5),body mass index (< 30, ≥30 kg/m2)parity (nulliparous, multiparous)age (< 40, ≥ 40 years old)center

First, a draft randomization list will be established by the methodologist and validated by the data manager. Then, the final randomization list will be performed and will be kept securely by the CEBIMER.

The follow-up data will be collected up to 10 days from delivery. This is not a blind study because of the galenic differences and the different methods of administration of the two treatments. As the induction of labor is necessary and justified for medical reasons, it is not possible to administer placebo.

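### As described, allocation after the first woman has no random element, so recruiting doctors in this open-label trial could guess the next arm better than chance; the text also conflicts on whether a randomization list exists

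*Protocol article*

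**What the plan says.** All of the allocation text is in the Trial design section of the protocol article.

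- Start of the sequence: "Randomization lists are not set up in advance and the first participant is randomly allocated".
- Everyone after the first: "For each following participant, the treatment allocation that minimizes the mismatch on the five selected factors between groups will be identified".
- The factors are Bishop score and body mass index, each in two classes, followed by "parity (nulliparous, multiparous)age (< 40, ≥ 40 years old)center".
- A list is nevertheless mentioned. A draft is drawn up by the methodologist and checked by the data manager, and "Then, the final randomization list will be performed and will be kept securely by the CEBIMER".
- Treatment is open: "This is not a blind study because of the galenic differences and the different methods of administration of the two treatments".
- The doctor who recruits also randomizes: "Written informed consent will be obtained from all participants by a study investigator (doctor) before randomization", and the same role logs on to the platform.
- Safeguards: "Randomization (ratio 1:1) will be carried out centrally", and "after a phase of verification of the eligibility criteria, the randomization will be performed automatically".

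The article gives no assignment probability and no rule for ties.

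**The concern.** Minimization without a random element makes each allocation a function of the earlier ones. In a masked trial with hidden records this matters little. Here each center sees its own past allocations, center is a balancing factor, and the person who could use a forecast is the one who decides whether to approach the woman. The Investigation sites section gives routine use of a second pessary as one of the reasons for choosing centers, so a preference between arms is plausible. A doctor with a forecast could offer the trial selectively. The resulting bias cannot be reliably removed in the analysis, and readers would question allocation concealment.

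The list sentences are a separate problem. A list generated beforehand cannot also be the source of allocations that depend on each new woman's characteristics, so the reader cannot tell which mechanism is in use.

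**Working it through.** **Plan's own figure.** The article gives no figure for predictability. Its only computable figure is the sample size: 55% versus 70%, two-sided 5%, 80% power. This gives 163 per group without a continuity correction and 176 with it, so the stated 176 reproduces. It does not bear on this point beyond supplying N = 360.

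**Inputs from the article.** 360 women, six centers, ratio 1:1, four two-level factors plus center, first allocation random, minimizing arm thereafter.

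**Assumptions.** Equal factor weights; ties broken at random; prevalences of one level of Bishop score, body mass index, parity and age of 0.40, 0.25, 0.50 and 0.06; equal center sizes. The imbalance measure is not stated, so two were used. Let D_k be the number in arm A minus the number in arm B among earlier women who share the new woman's level of factor k.

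- Range method: d = Σ_k (|D_k + 1| − |D_k − 1|)
- Sum method: d = Σ_k D_k

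If d < 0 arm A is preferred, if d > 0 arm B, and d = 0 is a tie. The preferred arm is given with probability p; p = 1 is the rule as written.

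**Results, range method (300 simulated trials per row).**

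| p | Ties | Correct guess, all records | Correct guess, own-center arm totals | 95th percentile of total arm imbalance |
|---|---|---|---|---|
| 1.0 | 16.4% | 91.8% | 64.1% | 2 |
| 0.9 | 15.8% | 83.7% | 61.6% | 2 |
| 0.8 | 14.8% | 75.7% | 59.0% | 4 |
| 0.7 | 13.6% | 67.4% | 56.0% | 6 |
| 0.5 | 4.5% | 50.0% | 50.0% | 38 |

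Check of the first row: determined allocations are guessed with certainty and ties half the time, so 0.836 × 1 + 0.164 × 0.5 = 0.918.

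**By state of the own center, p = 1 (600 simulated trials).** Each cell is the share of allocations, then the correct-guess rate.

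| Own-center imbalance | Range | Sum |
|---|---|---|
| 0 | 30.0%, 50.0% | 31.1%, 50.0% |
| 1 | 41.7%, 69.9% | 45.6%, 66.3% |
| 2 | 17.2%, 70.3% | 18.7%, 79.9% |
| 3 or more | 11.1%, 71.4% | 4.5%, 90.6% |

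The weighted averages are 64.1% (range) and 64.9% (sum). Guessing the opposite of the center's last allocation is right 59.8% of the time (range).

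**Sensitivity.** Center shares of 40/20/20/10/5/5% or prevalences of 0.50, 0.30, 0.70 and 0.04 moved the overall figures by 2 points or less. A separate simulation with shares of 30/20/20/10/10/10% gave 64.9% at p = 1, 59.3% at p = 0.8 and 56.1% at p = 0.7. Factor weights were not varied.

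**Does the timing window help a doctor?** Trial status reports 110 women randomized from 30 December 2016 to 22 October 2019, which is 1,026 days. The rate is 110 / 1,026 = 0.107 per day over all centers. The inclusion window of 24 to 36 h spans 12 h, in which 0.107 × 0.5 ≈ 0.05 other women would be randomized trial-wide, or about 0.01 per center. The next arm changes only when someone else is randomized, so waiting within the window almost never alters it.

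**The case against.** The strongest defense is that this is a condensed article. An assignment probability may sit in the full protocol, and withholding it from a text that sites can read would be sensible. The wording says that the minimizing arm is identified, not that it is always given. This stands in part: a random element may have been programmed. But the article does not merely stay silent. It attaches randomness to the first woman and a minimizing rule to the rest. If the platform does otherwise, the description is wrong.

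A second defense is that allocation is central, follows an eligibility check and is automatic, and that reasons for ineligibility or refusal are recorded for the flow diagram (Data collection and management). This prevents interference at the moment of allocation and leaves some trace of selective recruitment. It does not prevent a forecast made before consent is sought.

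Three stronger readings are tempting and are not supported:

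- That doctors can simply predict the next arm. One center does not hold the other centers' records, and about one guess in three would be wrong.
- That knowing parity, Bishop score and the other factors of the own center's women sharpens the guess. In the range-method simulation, the guess using own-center factor counts was right 62.8% of the time, no better than arm totals alone.
- That the choice of timing within the consent window is a practical route to manipulation. At the reported accrual it is nearly void.

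**Conclusion.** The point holds as a weakness in the stated allocation rule and as a contradiction in the text. Followed as written, the rule leaves about 84 to 87% of allocations after the first fully determined. It allows a correct guess about 64 to 65% of the time from own-center arm totals alone, rising to 70 to 80% when that center is out of balance by two. The route to bias is selective non-enrollment.

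These figures assume equal weights and random ties, and take the text at its word. The effect on the vaginal delivery comparison has not been estimated, and nothing in the document shows that bias has occurred. The conflict over randomization lists needs no assumption. The point is worth acting on during recruitment, because the remedy is cheap then and unavailable afterwards.

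**What to change.** 1. The sponsor should confirm with the coordinating data center what the platform does: the assignment probability, the imbalance measure, the weights and the tie rule.
2. If it is deterministic, give the minimizing arm with probability below 1 (for example 0.8, not disclosed to sites) and break ties at random. Apply this to all remaining allocations, 360 − 110 = 250 at the reported date, and document the date of the change.
3. If a random element already exists, leave the algorithm alone and correct the published description.
4. In either case, delete the draft and final list sentences, or state what those lists are for (for example, testing the algorithm).

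Cost: at p = 0.8, own-center guessing falls from about 64 to 59%, and guessing from full records from about 92 to 76%. The 95th percentile of total arm imbalance rises from 2 to 4 women, against 38 under simple randomization. The sample size is unchanged. The primary analysis in Statistical analysis is an unadjusted chi-square or Fisher test, so covariate adjustment should not be relied on to absorb the looser balance. A change of algorithm is also an amendment: Monitoring of the study requires agreement from the research team, sponsor and monitoring committee before submission to the ethics committee and the medicines agency.

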### Interventions

In the control group, 5 IU of oxytocin will be diluted in 49 ml of physiological saline and will be started at 2.5 mIU/min, a flow rate of 1.5 ml/h with an increase of 2.5 mIU every 20 to 30 min up to 12 ml/h. In case of abnormal fetal heart rate or abnormal uterine contractions, oxytocin will be stopped momentarily. In case of induction failure (cervical dilatation remaining < 3 cm despite 6 h of oxytocin = 1 syringe and the presence of regular uterine contractions and amniotomy), the patient must have a cesarean section. In total, oxytocin is administered to induce labor for 6 h and then if the labor begins, oxytocin can be continued for one more syringe in case there is a lack of uterine contractions or labor stagnation.

In the experimental group, the second Propess® must be removed after 24 h or earlier if labor begins, or in case of abnormal uterine contractions, abnormal fetal heart rate or poor material tolerance. If oxytocin is needed in the experimental group after 24 h of the 2nd Propess®, it should be delivered in the same way as in the control group. If the labor does not begin (cervical dilatation remaining < 3 cm despite second Propess® + 6 h of oxytocin = 1 syringe and the presence of regular uterine contractions and amniotomy), the patient must have a cesarean section. In case the second Propess® falls off, a 2-h-long wait is tolerated. If labor does not start and if the fall occurred before 18 h of use, another Propess® should be inserted for a duration which should not exceed 24 h of cumulative exposure. In case it falls after 18 h of use, induction of labor should continue through oxytocin.

Both treatments will be labeled and supplied to the different centers and stored according to the manufacturers’ recommendations: between − 10 and − 20 °C for Propess® and between + 2 and + 8 °C for oxytocin. A regular temperature verification must be done to ensure the good conservation of the products. Antalgic medications are authorized. Only Risordan® and Natispray® are allowed to correct abnormal uterine contractions. No other medical or mechanical labor-inducing means are permitted.

### Participant’s timeline

A brief Standard Protocol Items: A Schedule Of Enrolment, Interventions, And Assessments (in accordance with the Recommendations from Interventional Trials (SPIRIT)) is provided in Fig. 1.

**Fig. 1 Fig1:**
[figure not shown]
SPIRIT figure. Schedule Of Enrolment, Interventions, And Assessments. ** H = hours; D = days. AE = adverse events / SAE = serious adverse events. ^1^ Complete blood counts, blood coagulation and search of irregular agglutinin. ^2^ By the midwife

### Sample size calculation

The number of participants is based on the primary outcome calculation for a comparative superiority test. Based on a local retrospective study (55% vaginal delivery rate after Propess® and 70% after two Propess® placements and Syntocinon®) performed prior to that of Antonazzo [13], the 15% between-group difference indicates that to afford an 80% power to detect a specific difference at the 5% significance level (two-sided test), 176 patients per group are required in a two-group scenario (nQuery Advisor 7). As the rate of non-evaluable patients (early drop-out, violation of inclusion or exclusion criteria, lack of compliance, intercurrent illness, comedication which was not allowed by the protocol) is expected to be very low in this study due to the nature of the primary outcome (vaginal delivery), we believe that a total of 360 (180 per group) will be an adequate sample size for the study.

### Data collection and management

Data on every outcome will be collected via an electronic case record form (ECRF) built by the Center for Epidemiology, Biostatistics and Research Methodology (CEBIMER) of the University Hospital of Limoges with the software CLINSIGHT (CLINSIGHT company). ERCFs will be completed by the investigator and a clinical trial technician. This database will be hosted on a server dedicated to CEBIMER CHU Limoges in secure premises. The promotor (University Hospital of Limoges) will have access to all data. A daily backup of the database will be performed. Periodic data completeness and quality checks will be performed by the study team by means of internal audits.

As it is anticipated that participants will only stay in the hospital for a maximum of 10 days after delivery, there are no strategies in place for collecting other outcome data. The reasons for not being eligible or not wanting to take part in the study will be recorded and reported in a CONSORT flow diagram, but the data for these participants will not be collected for analysis.

Patients withdrawing their consent after randomization will be noted in the CONSORT Flow-Chart and we will perform analyses intended to treat. In accordance with Law No. 2002–303 of March 4, 2002, patients will have access to the overall results of the research at their request.

### Serious adverse events

Serious adverse events (SAEs) will be any medical occurrence that results in death, is life-threatening, causes or prolongs hospital admission, results in persistent or significant disability or incapacity, or results in congenital anomaly. In the study protocol, maternal and fetal/neonatal SAEs will be divided into a group of “expected SAEs” explained by and related to the two treatments (Propess® and oxytocin) and “unexpected SAEs”. An immediate notification of all of these SAEs must be sent by the investigator to the local Clinical Trial Vigilance Unit and the promotor. Each year, the promotor sends to the “Agence Nationale pour la Sécurité du Médicament et des Produits de Santé” (ANSM) and to the Committee for the Protection of Person (CPP) a safety report of the SAEs.

### Monitoring of the study

A project leader of the Medical Affairs and Innovation Department will be responsible for the coordination and management of the trial (regulation, general coordination of the study, financial and administrative management, monitoring of inclusions). A clinical research associate monitor is sent regularly to each center by the promotor. There is a monitoring plan defining the frequency of the visits and the elements to monitor: consents, principal outcome, eligibility criteria, adverse events and SAEs, treatments.

The establishment of an independent monitoring committee was decided because the study involves pregnant women using a drug outside the marketing authorization. This committee, composed of three people outside of the Limoges University Hospital (one obstetrician gynecologist and two pharmacologists) met at the start of the study and will meet every 60 patients. The committee is there to ensure the absence of unbalanced treatment that may lead to an excess of morbidity and mortality in the groups. So, the role of this independent monitoring committee is to monitor the study data and safety of participants. The opinion of the committee is conveyed to the promotor (University Hospital of Limoges) and the project team.

Thus, any amendment to the protocol must be approved by the research team, the promotor, and the monitoring committee before being submitted to CPP and ANSM.

### Statistical analysis

Data will be analyzed by the UVEC (pharmacovigilance unit) for security and vigilance analyses and local CEBIMER for the main statistical analyses using SAS 9.3 (SAS Institute Cary, NC). *p* values < 0.05 will be considered statistically significant. Our analysis will be conducted using the intention-to-treat principle and reporting will follow CONSORT 2010 recommendations.

Descriptive statistics of continuous data will be reported as means ± standard deviations or medians and interquartile ranges depending on the distribution of the variable. Dichotomous and categorical data will be presented by numbers and percentages. The primary outcome will be reported with numbers and percentages in each group. The analysis of the primary outcome will be conducted by comparing the proportions of vaginal delivery between the two groups with the use of a Chi-square or Fisher’s exact test depending on the theoretical numbers. The effect seize will be estimated using odds ratio and its 95% confidence interval.

Secondary analyses will be computed in order to compare failure induction of labor, maternal and fetal morbimortality between the two groups of randomization by using a Chi-square or a Fisher’s exact test depending on the theoretical number for dichotomous or categorical outcomes and a Student’s *t* test or a non-parametric Mann–Whitney test for continuous outcomes depending on the distribution of the variable.

We will use the Shapiro–Wilk test for testing whether variables are normally distributed.

All data analysis will be performed unblinded according to a pre-established statistical analysis plan drafted prior to access to the data and reported in a document signed by all authors. This statistical analysis plan will be updated before data lock for the final analysis.

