The induction process is evaluated using the Bishop score [19], which considers the length, dilatation, position, and consistency of the cervix and the height of the mobile fetus. The score predicts the success of term labor induction [20]. A score < 6 is considered poor. Some teams define a score ≤ 3 as very poor, 4–5 as rather poor, and ≥ 6 as good [21]. Some professionals advocate the use of objective cervical ultrasound [22, 23], but this practice remains controversial [24]. Other predictors of the success of induction include multiparity, higher gestational age (> 41 + 4 WG) [25], maternal age (< 35 years) [26], and body mass index (< 30 kg/m^2^) [27, 28].

The recommendations regarding cervical ripening differ in terms of the chemicals used, route of administration, dosage, and monitoring modality. Mechanical induction is employed in 50% of maternity hospitals [18]. The double balloon (Cook®) is a single-use device placed for up to 12 h. The Foley® catheter is a single balloon catheter (n°18), and the Dilapan® is a cervical dilator.

Hormones are commonly used to induce labor. Oxytocin, in combination with amniotomy, is employed if the cervix is considered favorable (Bishop score ≥ 6), reducing the interval between induction and delivery [29]. If the cervix is unfavorable, oxytocin is also used to trigger labor but is not the first choice [29]. Natural (Propess®, Prostine®, and Prepidil®) and synthetic (Misoone®, Gymiso®, Nalador®, and Cervagem®) PGs have been used since 1968 to induce cervical ripening if the Bishop score is < 6.

PGs are widely used in France [30]. The Propess®, a vaginal patch featuring progressive continuous diffusion of 10 mg dinoprostone (0.33 mg/h), is placed for 24 h. Propess® use has increased greatly over time, from 10.2% [30] of maternity hospitals in 2001 to 89.1% today [10].

Dinoprostone in various forms (Propess®, Prostine®, and Prepidil®) exhibits a very good risk-to-benefit ratio [7]. According to the Higher Health Authority, intravaginal forms should be favored if PGs are used to induce labor [1]. Furthermore, the Propess® can obviously be removed at any time if uterine hypertonia (which may trigger fetal repercussions) develops, unlike prostaglandin gels (Prostine® and Prepidil®), which cannot be removed.

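### Allocation is minimized on five factors but the primary test ignores them, so to the extent they are prognostic the test is conservative and some precision for the marginal effect is forgone

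*Protocol article*

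**What the plan says.** **Allocation.** Protocol article, Trial design: "It will be a randomization by minimization on the following factors", namely Bishop score (two bands), BMI (cut at 30), and "parity (nulliparous, multiparous)age (< 40, ≥ 40 years old)center". For every woman after the first, "the treatment allocation that minimizes the mismatch on the five selected factors between groups will be identified".

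**Prognostic status.** The Background says that the Bishop score predicts the success of induction, and adds: "Other predictors of the success of induction include multiparity", followed by gestational age, maternal age (cut at 35) and BMI (cut at 30). For nulliparous women it cites a risk of induction failure of 50% with a very unfavorable score and 10% with a score of 4–6. Center is not described as a predictor.

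**Analysis.** Statistical analysis: the primary outcome is analyzed by "comparing the proportions of vaginal delivery between the two groups with the use of a Chi-square" or Fisher's exact test, and the effect is "estimated using odds ratio and its 95% confidence interval". No covariate or stratum is named there, and no adjusted analysis is mentioned for the primary or secondary outcomes. That the odds ratio is crude is inferred from this.

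**Sizing.** Sample size calculation: 55% against 70% vaginal delivery, where "the 15% between-group difference indicates that to afford an 80% power to detect a specific difference" at the two-sided 5% level, giving 176 per group, raised to 180.

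**The concern.** The ordinary variance of a difference in proportions assumes that prognostic factors can differ between arms by chance. Minimization largely removes that source of variation. If the factors predict vaginal delivery, the usual standard error then exceeds the real sampling variation. The test rejects less often than 5% under the null, and the interval for the marginal effect covers more than 95%.

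At stake is efficiency: precision obtained through the allocation is not used, in a trial whose recruitment has already had to be extended. A related point is that the trial is sized on a difference of 15 percentage points, but the only effect measure planned is an odds ratio. This is not a detail left to an unseen SAP, because the protocol article itself names the test and the effect measure.

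**Working it through.** **1. Reproduce the plan's sample size.** Inputs from the Sample size calculation: p₀ = 0.55, p₁ = 0.70, mean 0.625, difference d = 0.15, two-sided 5%, 80% power.

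- Uncorrected: n = [1.96·√(2·0.625·0.375) + 0.842·√(0.55·0.45 + 0.70·0.30)]² / 0.15² = 162.3, so 163 per group.
- With continuity correction: (n/4)·[1 + √(1 + 4/(n·d))]² = 175.4, so **176 per group**, an exact match.

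The size therefore fits an unadjusted, continuity-corrected comparison.

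**2. Power of the plain chi-square at 180 per group.**

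- SE under the null: √(0.625·0.375·2/180) = 0.0510.
- SE under the alternative: √((0.2475 + 0.21)/180) = 0.0504.
- Power: Φ[(0.15 − 1.96·0.0510)/0.0504] = Φ(0.991) = 83.9%.

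**3. Effect of ignoring balanced factors.** Let R² be the share of outcome variance that the five factors explain. The documents do not give it, so a range is assumed. With close balance, the true SE of the difference is the nominal SE times k = √(1 − R²).

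- True level of the unadjusted test: 2·[1 − Φ(1.96/k)].
- Interval width ratio: 1/k.
- Power, unadjusted: Φ[(0.15 − 1.96·0.0510)/(0.0504·k)].
- Power, adjusted: Φ[(0.15 − 1.96·0.0510·k)/(0.0504·k)].

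| R² (assumed) | True level, unadjusted | Interval too wide by | Power, unadjusted | Power, adjusted |
|---|---|---|---|---|
| 0 | 5.0% | 0% | 83.9% | 83.9% |
| 0.05 | 4.4% | 2.6% | 84.5% | 85.7% |
| 0.10 | 3.9% | 5.4% | 85.2% | 87.5% |
| 0.20 | 2.8% | 11.8% | 86.6% | 91.0% |

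**4. Simulation check.** 360 women, six centers, minimization on the five factors, 3,000 trials per scenario; factor prevalences and effects are assumed. Near 5%, the Monte Carlo standard error is about 0.4 points.

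| Factor effects (assumed) | Level, unadjusted | Level, adjusted | Power, unadjusted | Power, adjusted |
|---|---|---|---|---|
| None | 4.9% | 5.1% | 84.7% | 85.1% |
| Mild | 5.2% | 6.1% | 83.7% | 85.0% |
| Moderate | 3.3% | 4.9% | 85.2% | 88.2% |
| Strong | 1.9% | 5.1% | 85.8% | 91.4% |

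Under the null, the real standard deviation of the risk difference was 0.0487 (moderate) and 0.0459 (strong), against an average nominal SE of 0.0523. The crude odds-ratio interval covered 96.7% and 98.1%. In the mild scenario there is no clear difference: the adjusted test's level there is somewhat above 5%, so its 1.3-point power advantage is no evidence of a real gain.

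**5. Odds-ratio scale.** At the planning values the crude OR is (0.70/0.30)/(0.55/0.45) = 1.91. With 99 and 126 events of 180, the SE of its logarithm is √(1/99 + 1/81 + 1/126 + 1/54) = 0.22. In simulations with assumed factor effects, the adjusted log-OR has a larger SE, about 0.23–0.26. The conditional OR is also larger (2.06 moderate, 2.26 strong), and the adjusted test gains power for that reason, not through a narrower interval.

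**The case against.** The case for leaving the plan alone is that a conservative primary test endangers no conclusion. Several parts of it stand.

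- **No inflation, no shortfall.** A reader might infer that the 5% level is breached or that the trial is underpowered. Neither follows. The error is in the conservative direction, and the unadjusted test keeps about 84–86% power at 360 against the stated 80%. Power is forgone only relative to an adjusted analysis.
- **Prognostic strength is unknown.** A reader might take the Background to call all five factors strong predictors. It does not use that word, it does not list center, and its age cut (35) differs from the one used for allocation (40). Its 50% against 10% gradient concerns induction failure in nulliparous women, not vaginal delivery. The size of the effect therefore rests on assumed R² values, and with weak factors it disappears.
- **Too wide on which scale?** A reader might infer that adjustment would narrow the planned odds-ratio interval. On the log-OR scale the adjusted standard error rises. The gain in width holds for the marginal effect, such as a standardized risk difference.
- **Effect measure.** Numbers and percentages per group will be reported, so the difference can be read off. But no interval is planned for it.
- **The SAP might already adjust.** It is not shown and is to be updated before data lock. That does not remove the mismatch in the published text, which states the primary test outright.

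**Conclusion.** The concern holds as a point of efficiency and coherence: the stated primary analysis leaves out the factors used to allocate. If these explain 5–20% of the variance in vaginal delivery (assumed), the nominal 5% test runs at about 4.4–2.8%, the risk-difference interval is about 3–12% too wide, and about 1–4 power points are forgone at 180 per group. The strong simulated scenario gives nearly 6 points (91.4% − 85.8%). The loss is negligible if the factors are weak. It is worth changing because the remedy is cheap, not because the planned test is invalid.

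**What to change.** Before outcome data by arm are examined (the article says that the analysis is unblinded):

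1. Make the primary analysis a logistic regression on arm plus the five minimization factors. Pool the closed low-recruiting center with another small center so that sparse categories do not destabilize the model.
2. Report the standardized (marginal) risk difference with its 95% CI from that model as the main effect measure, because it matches the 15-point difference used for sizing.
3. Give the odds ratio second, labelled as conditional, noting that it will be larger than the crude one and that its interval need not be narrower.
4. Keep the chi-square or Fisher test as a supportive analysis.

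**Cost.** A change of wording in the protocol and SAP, and slightly more analysis work. If it is handled as a protocol amendment, the approval route in the Monitoring section applies. No extra data or patients are needed, since the factors must be known to run the minimization.
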